##### Analyses

The specific analyses and hypothesis tests (which are preliminary because this is a feasibility study) will assess effectiveness of the brief intervention and ENCOMPASS on substance use outcomes. These data will be used to generate hypotheses about brief and comprehensive interventions for a future larger study.

##### Sample size and power

We plan to recruit n = 80 youth and caregiver dyads per county (160 total). We estimate that no more than 10% of youth in each county will be high-risk, resulting in a sample size of n = 16 assigned to ENCOMPASS and n = 144 to first-stage brief intervention (BI). We anticipate 20% loss at 6-month follow-up resulting in n = 12 in the ENCOMPASS group and n = 116 in the first-stage BI with 6 month data (58 responders and 58 non-responders, assuming a 50% response rate. We have accounted for a sample size inflation factor related to potential within-county intraclass correlation (ICC) of outcomes. Specifically, in the first step of the back-calculation, we determined that a sample size of n = 40 per responders and non-responders to the first-stage intervention (with 6-month data) is required under the “independence of observations” assumption (i.e., *before* accounting for clustering) to provide 80% power for the two-sided model-based tests to detect an effect size (0.63) that is between medium (0.50) and large (≥ 0.80). For a first-stage effective sample size of 40 in each group (responder vs. non-responder), there is a 1.39 sample size inflation factor (IF) when the ICC = 0.01 and the number of clusters (i.e., counties) = 2: IF = [1 + (average 40 patients per cluster − 1) × ICC of 0.01]. Therefore, an actual sample size of 56 per first-stage brief intervention (i.e., 40 × 1.39) with 6-month data is required (i.e., an effective sample size of 40 per first-stage brief intervention with 6-month data if observations were not clustered). The sample of 56 in each group will provide adequate power for this feasibility study and its preliminary hypothesis tests, given that we anticipate n = 58 per first-stage group (responder vs. non-responder) with 6-month data. This power calculation is conservative because the longitudinal models will have slightly increased power due to incorporating all available data (baseline, 3-months, 6-months), including data from persons missing one but not all times points. The goal will be to estimate effect sizes, for which the planned sample size will be adequate. A minimum of 12 per group is recommended for estimating effects sizes of continuous outcomes in pilot or feasibility studies [44].

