### Data analysis

#### Measurement of intervention effectiveness and treatment response

##### Preliminary analyses

Preliminary analyses will be used to compare the primary treatment response outcome (confidence of abstaining measured by the BSCQ) and substance use outcome across the responders and non-responders of the brief intervention and ENCOMPASS at baseline, 3 months, and 6 months. A separate model will be utilized to measure effectiveness among those assigned to ENCOMPASS. Substance use will be calculated as number of days in the past month of using alcohol, marijuana, and other substances (range 0–90). These outcomes will be compared between groups with longitudinal generalized linear models (GLM) using the GENMOD procedure with a linear link and normal error distribution. The BSCQ and substance use outcome will be analyzed in separate models. The baseline measure of BSCQ or substance use days will be adjusted as covariates and the repeated measurements of each outcome at 3 months and 6 months will be analyzed simultaneously in the model.

The GLMs are easily fit for non-Gaussian distributions by specifying appropriate link functions and error distributions. If substance use days exhibit sparse counts or large frequency of zeros, we will consider using logistic, Poisson, or zero-inflated Poisson regression models, depending on the observed distributions of outcome behaviors. We also will explore analyzing substance use as time-to-event data using a Cox proportional hazards regression model with the SAS PHREG procedure with censoring if loss to follow-up occurs. Effect sizes will be computed from the model as differences between groups on adjusted means divided by SDs for the linear models, or differences between odds for logistic models or hazards for Poisson models.

The median and relevant percentile (e.g. 25th or 75th) of time to events will be presented by group with associated confidence intervals. All models will include an indicator variable for whether the subject was enrolled as a detained or probation youth. Other covariates will be included based on their theoretical importance as potential confounders and on their imbalance between randomized arms at baseline. We also will examine moderators that we have hypothesized to be potential determinants of treatment response (e.g., family functioning).

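### The county inflation factor is computed with the pre-inflation cluster size of 40 rather than about 58, so 56 per group is not an effective 40; the slip lies in the calculation and does not show an underpowered comparison

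*Protocol article*

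**What the plan says.** All the sample size figures are in the protocol article, section Sample size and power. Before clustering, the plan requires "n = 40 per responders and non-responders to the first-stage intervention" to give "80% power for the two-sided model-based tests" at a standardised effect of 0.63. It then inflates for clustering within county, stating that "there is a 1.39 sample size inflation factor" "when the ICC = 0.01 and the number of clusters (i.e., counties) = 2", by the rule "IF = [1 + (average 40 patients per cluster − 1) × ICC of 0.01". This turns 40 into 56 per group, which the plan equates with 40 unclustered observations. It anticipates 116 youth with 6-month data, 58 in each response group, and concludes: "The sample of 56 in each group will provide adequate power for this feasibility study and its preliminary hypothesis tests". Recruitment is 80 dyads in each county.

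On the models, the section Preliminary analyses states: "All models will include an indicator variable for whether the subject was enrolled as a detained or probation youth". Further covariates are to be chosen by theoretical importance and baseline imbalance. No county term is named for the effectiveness outcomes.

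**The concern.** A design effect of the form 1 + (m − 1) × ICC depends on m, the number of youth actually analysed in each cluster. The plan defines the cluster as the county but sets m from the sample before inflation. Inflating the sample also enlarges the two counties, and that enlargement is never fed back into the formula. The printed factor therefore does not belong to the printed sample.

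There is also a mismatch between sample size and analysis. The sample is inflated for correlation within county, but the description of the models does not say how county will be handled.

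At stake is the correctness of the stated power. The section headed Analyses says the data will serve to generate hypotheses for a larger study. The same method reused there with larger counties would carry a larger error.

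**Working it through.** **Inputs from Sample size and power:** effect size 0.63; 80% power, two-sided; 40 per group before clustering; ICC 0.01; 2 counties; 56 per group required; 116 in total (58 per group) anticipated; 80 dyads recruited per county.

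**Assumptions:** alpha is not stated; 0.05 two-sided is assumed because it reproduces the plan's 40. Equal recruitment is taken to give equal numbers analysed per county.

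**1. Reproducing the plan.**
- n per group = 2 × [(1.96 + 0.8416) / 0.63]² = 39.55, rounded up to 40.
- Power at 40 per group is 80.4% by normal approximation and 79.5% by noncentral t.
- Inflation factor = 1 + (40 − 1) × 0.01 = 1.39, and 40 × 1.39 = 55.6, rounded up to 56.

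All three of the plan's figures (40, 1.39, 56) reproduce.

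**2. Where the 40 per county comes from.** Two groups of 40 make 80, and 80 / 2 counties = 40. The sample the plan expects gives 116 / 2 = 58 per county. The sample it requires gives 112 / 2 = 56 per county.

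**3. The plan's formula with its own county sizes.** The effective n is the n per group divided by the inflation factor.

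| n per group | Youth per county | Inflation factor | Effective n per group | Power for 0.63, t | Power for 0.63, normal |
|---|---|---|---|---|---|
| 58 (anticipated) | 58 | 1 + 57 × 0.01 = 1.57 | 58 / 1.57 = 36.9 | 76.2% | 77.3% |
| 56 (required) | 56 | 1 + 55 × 0.01 = 1.55 | 56 / 1.55 = 36.1 | 75.2% | 76.4% |

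At 58 per group the fall from the pre-clustering calculation is about 3 points by either method: 79.5% to 76.2%, or 80.4% to 77.3%.

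**4. Could another cluster definition explain the 40?** If a cluster were one response group within one county, its size would be 58 / 2 = 29. The factor would be 1 + 28 × 0.01 = 1.28, the effective n 58 / 1.28 = 45.3, and power 84% by t. The plan's 40 is neither 29 nor 58, and the plan itself identifies clusters with counties.

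**5. Does this design effect apply to the contrast?** It is the right penalty when whole clusters belong to one group or the other. Here each county contains both responders and non-responders. With similar proportions in each county, a shared county effect enters both group means and cancels from their difference.
- With no inflation, 58 per group gives 92.0% power for 0.63 by t, and 80% power for 0.525 SD.
- A simulation with ICC 0.01, two counties, 58 per group balanced across counties and no county term gave about 92% power and 4.8% type I error.

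**The case against.** The strongest reply is that the slip is an under-correction inside a penalty that was not needed. On this view the plan over-protected itself, and nothing in the trial suffers. That stands as far as real power is concerned. A reader might infer from the 76% that the trial will miss its stated power, or that more youth should be enrolled. The documents do not support either inference, because both response groups come from the same two counties. The study is also described as a feasibility study with preliminary tests, and its stated goal is to estimate effect sizes.

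A second reply is that the absence of a county term is an argument from silence. The covariate list is open, and a condensed article may leave the full list to a longer document. This also stands in part. One may say that the article names no county term although it inflates for county; one may not say that the analysis will ignore county. Nor does any passage suggest that response rates differ by county. Under an assumed unequal split of 40/18 against 18/40, simulation at ICC 0.01 without a county term still gave 91% power and 5.8% type I error, so the consequence at the plan's own ICC is small.

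What neither reply removes is that the printed formula, cluster size and sample disagree within one section. If the inflation is kept, 1.39 is the wrong factor. If county is adjusted for, the inflation does not belong there.

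**Conclusion.** The point holds as an internal error in the calculation. By the plan's own formula, its anticipated sample has an inflation factor of 1.57 and is worth about 37 per group (about 36 at the required 56). The corresponding power for 0.63 is about 76% (75%) by t-test, or 77% (76%) by normal approximation. The statement that 56 per group equals an effective 40 is wrong. These figures rest on alpha 0.05 two-sided, the plan's ICC of 0.01, and equal numbers analysed in the two counties.

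They are what the formula yields and are not an estimate of the trial's real power. For a contrast within counties, about 92% at 58 per group is the better figure. The unnamed county term is a secondary point about consistency between sample size and analysis. Severity is minor to should-fix.

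**What to change.** In Preliminary analyses, name county as a fixed effect in the brief-intervention outcome models that compare responders with non-responders. In Sample size and power, drop the inflation factor and the claim of an effective 40. State instead that, with county adjusted for, 58 per group with 6-month data gives about 92% power for an effect of 0.63, or 80% power for about 0.53 SD (0.525 before rounding). State the alpha used.

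Keeping a corrected factor of 1.57 alongside a county fixed effect would be inconsistent and should be avoided. Enrolment stays as planned. The cost is one rewritten paragraph and one model term (1 degree of freedom).

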#### Measurement of implementation in juvenile justice and CMHC settings

We will utilize both qualitative and quantitative methods to assess implementation of substance use screening in the juvenile justice systems and implementation of interventions in the CMHCs.

##### Stages of implementation completion exploratory analyses

We will utilize the stages of implementation completion (SIC) tool to track and assess implementation progress separately for the CMHCs and juvenile justice settings. Utilizing the online SIC tracker, we will log data occurring at each of the implementation stages: pre-implementation (exploration and preparation), implementation, and sustainability. The online SIC tracker computes SIC scores at each implementation stage for measures such as proportion (percentage of planned activities performed) and duration (number of days between activities), which have been shown to predict successful achievement of implementation milestones [45, 46]; data also provides insights into organizational implementation behavior predicting sustainment.

##### Quantitative analysis

We will conduct separate analyses for juvenile justice systems and CMHCs based on CMHC and juvenile justice staff completion of implementation measures (see Table 1 for complete list of measures). We will use linear mixed models to analyze repeatedly measured implementation variables (baseline/pre-implementation, 6 months/post-implementation) to determine whether implementation variables change over time. In one model measuring implementation of substance use screening in juvenile justice settings, organizational readiness to implement change (based on juvenile justice staff self-reports) will serve as the dependent variable and staff and setting characteristics (e.g., demographics, years of experience, see Table 1) will serve as independent variables. Similar analyses will be conducted to assess implementation with the CMHCs.

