### Study setting

Two counties in a Midwest state were chosen based on high rates of substance-related arrests and rates of substance use among adolescents in the community. Counties were chosen given their small size as well as the presence of one primary community mental health center (CMHC) that is designated to serve the community. This allows for feasibility of building and strengthening relationships between juvenile justice and community mental health professionals/agencies.

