#### Community partner participants

Community partner participants will be clinicians, case managers, and supervisors working in the CMHC in each county (range n = 10–30). Bachelor’s level case managers from each CMHC site (n = 2 case managers for each county) will be recruited to act as intervention specialists. They will be trained in the brief intervention and provide treatment to YIJJ and their caregivers. Master’s level licensed clinicians from each CMHC (n = 2 for each county) will be trained in the comprehensive substance use intervention and provide treatment to YIJJ.

The juvenile justice system in each county have agreed to participate and implement substance use screening. Designated juvenile probation officers/intake officers will be identified and will be responsible for conducting universal substance use screening with all youth coming through the detention center at intake.

In addition to these primary individuals who will provide interventions, we will seek participation from other personnel (e.g., juvenile justice intake staff, CMHC supervisors) who are involved in the implementation and sustainability of the interventions to complete qualitative interviews and quantitative measures to assess feasibility and implementation in these settings.

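### With one justice system and one CMHC in each of two counties, any setting characteristic that is constant within a setting is fully confounded with county in the implementation models

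*Protocol article*

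**What the plan says.** The Quantitative analysis section, under measurement of implementation, says: "We will conduct separate analyses for juvenile justice systems and CMHCs". Linear mixed models are to be fitted to implementation measures taken before and after implementation, "to determine whether implementation variables change over time". One model is then spelled out for the justice side. Readiness for change, as reported by justice staff, is the outcome, and "staff and setting characteristics (e.g., demographics, years of experience, see Table 1) will serve as independent variables". Similar analyses are planned for the CMHCs.

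The number of settings follows from two other sections. Study setting says "Two counties in a Midwest state were chosen", and gives as one reason for the choice "the presence of one primary community mental health center (CMHC) that is designated to serve the community". Community partner participants adds: "The juvenile justice system in each county have agreed to participate and implement substance use screening".

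In Table 1, the system-level implementation rows list scales of implementation climate, leadership and citizenship behaviour and of readiness for change, completed by CMHC staff, justice staff and supervisors. The demographics row names youth and parent as the only informants.

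**The concern.** A regression can attribute differences in readiness to a feature of the setting only if settings that differ on that feature can be compared while other differences between settings are averaged out. Here each model has one setting per county. Anything fixed within a setting, such as local policy, size or staffing level, changes only when the county changes.

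A model fitted to staff-level records will still return a coefficient and a p-value for such a variable if county is not in the model. It does so by treating staff as replicates of the setting. The output would look like evidence that a particular setting feature drives readiness, when it shows only that two counties differ.

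This matters because identifying facilitators and barriers to implementation is a stated objective of the hybrid type 1 design. The Limitations section mentions the two small counties only in terms of whether the model carries over to larger ones. It does not raise the confounding of setting with county.

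**Working it through.** The article gives no sample size, power or significance level for these models, so there is no figure of its own to reproduce. The check has three parts.

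**1. What can be identified.**

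Inputs: 2 counties (Study setting); 1 primary CMHC per county (Study setting); 1 justice system per county (Community partner participants); separate models for the two sectors (Quantitative analysis). Each model therefore has 2 settings. Fixed-effect design matrices were built for 2 counties × m staff × 2 time points, with m = 5, 10, 15 and 30. The ranks were the same for every m:

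| Columns | Number of columns | Rank |
|---|---|---|
| intercept, county, setting variable | 3 | 2 |
| intercept, setting variable 1, setting variable 2 | 3 | 2 |
| intercept, county, staff covariate, time | 4 | 4 |
| intercept, county, setting variable, staff covariate, time | 5 | 4 |

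The first two rows show that there is one between-setting contrast at most and that it is the county contrast. With an intercept and that contrast fitted, 2 − 2 = 0 between-setting degrees of freedom are left. The third row shows that staff covariates and the pre/post effect are estimable with two counties. The fourth shows that adding time does not rescue a county-constant variable. More staff do not help either.

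**2. Size of the error if county is ignored.**

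Let m be staff per county and ICC the county-level intraclass correlation of the staff measure. The ratio of the true variance of the county contrast to the variance that the staff-level analysis assumes is

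ratio = [ICC + (1 − ICC)/m] / [(1 − ICC)/m] = 1 + m × ICC/(1 − ICC),

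and the approximate true two-sided error of a nominal 5% test is 2 × [1 − Φ(1.96/√ratio)].

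Example, m = 20 and ICC = 0.05: ratio = 1 + 20 × 0.05/0.95 = 2.05; 1.96/√2.05 = 1.37; error = 0.171.

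| Staff per county | ICC 0.01 | ICC 0.05 | ICC 0.10 |
|---|---|---|---|
| 10 | 0.062 | 0.113 | 0.177 |
| 20 | 0.074 | 0.171 | 0.275 |
| 30 | 0.086 | 0.222 | 0.346 |

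Both inputs are assumptions. The article's ICC of 0.01 is for youth outcomes, and none is given for staff measures. Its range of 10–30 is for CMHC staff and could be read per county or in total; no number is given for justice staff. If 10–30 is the total, m is 5–15 and the same formula gives about 6–7%, 8–14% and 12–23% at the three ICCs. A design-effect version, with ratio 1 + (m − 1) × ICC, gives similar values: 0.084 at m = 30 and ICC 0.01, and 0.321 at m = 30 and ICC 0.10.

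**3. The cross-reference.**

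The predictor sentence sends the reader to Table 1 for demographics and years of experience. The only demographics row there is for youth and parents, and years of experience does not appear in the table.

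**The case against.** The strongest reply is that the article names no county-constant predictor. Its bracketed examples, demographics and years of experience, can be staff-level. The climate and leadership scales in Table 1 are rated by individual staff, and the Implementation model section counts organisational climate as inner context, so these scales are a natural reading of setting characteristics. They vary among staff in the same county, and their within-county associations remain estimable. This stands, and it sets the limit of the point: the aliasing applies only to variables that are constant within a setting. It would be wrong to conclude that every setting-related predictor must be dropped.

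It does not dispose of the point. The text names setting characteristics as well as staff characteristics, and the Implementation model section also lists staffing and local policy among the context factors. Nothing in the analysis section excludes predictors of that kind. The limit comes from the design, so a fuller analysis plan could not remove it.

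A second reply is that the error rates describe an analysis to which the article does not commit, since the random-effects structure is left open. That is fair. The rates illustrate a risk and are not a property of the plan. The identification result does not depend on them.

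A reader might also infer that the models leave out time, so that change is never tested. The article does not support this. The sentence before the predictor list plans mixed models on pre and post measures for the stated purpose of assessing change, and the list given for the one model is not said to be complete. That the time term is not repeated there is a matter of wording.

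**Conclusion.** The point holds for predictors that are constant within a setting. With two settings per model, such a characteristic cannot be separated from county or from any other such characteristic, whatever the number of staff. This rests only on the stated numbers of counties, CMHCs and justice systems and on the separate models.

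How far a test that ignores county would exceed 5% depends on the assumed staff ICC and staff numbers. It ranges from about 6% to 35% over the values shown. The point does not extend to staff-level characteristics, to individually rated scales, or to the pre/post effect, all of which are estimable. The missing explicit time term and the Table 1 reference are clarifications of lesser weight.

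**What to change.** In each sector's model:

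- Enter county as a fixed two-level factor.
- Restrict predictors to those that vary among staff within a county: staff demographics, years of experience, and individually rated climate and leadership scales.
- State that county-constant setting characteristics will not be tested, and describe them narratively with the SIC and interview data, both of which are already planned.
- Name the pre/post term explicitly as the effect that answers the question about change.
- Correct the Table 1 reference by adding staff demographics and years of experience, with staff as informants. The article says data collection has not started, so these items can still be included.

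The cost is a few sentences of analysis text and one line in Table 1. What is given up is regression estimates for county-constant characteristics, which two counties cannot identify in any case.
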